**Secondary**

2. To compare caregivers' perception of helpfulness in communicating with their physicians between the QPS and the GIS.
3. To examine the level of patients' and caregivers' overall satisfaction with the consultation with the use of the QPS versus the GIS.
4. To examine physicians' views about the information material and overall satisfaction with the use of the QPS versus the GIS.

5. To explore how the use of QPS affects the average speaking time of patient or physician during the consultation visit.
6. To establish demographic and clinical predictors of patients' perception of helpfulness of a QPS
7. To examine the overall patients' preference between the QPS and GIS in an open label phase.
8. To compare the change in patient anxiety state with the use of the QPS versus the GIS.
9. To explore the factors underlying patients' preferences for the QPS or GIS.

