## E6. Study Procedures

The research staff will first identify a potentially eligible candidate by screening all scheduled patient consultations on that day, and then inform and obtain a verbal consent from the attending physician for the patient's participation in the study. After the routine nurse assessment, the

research coordinator will obtain patient's written consent and then ask him/her to complete the Spielberger State Trait Anxiety Inventory (**Appendix A**), 2 questions from Cassileth Information Styles Questionnaire (**Appendix B**), and the Control Preferences Scale (**Appendix C**). The patient will then be randomized to receive either the QPS (**Appendix D**) or the GIS (**Appendix E**). It will take approximately 5 minutes to read through the QPS or GIS. The questionnaires should take about 5 minutes to complete. Caregivers accompanying patients to the clinic who are willing to participate in the study will also be asked to provide consent and will be given the same information material (either QPS or GIS). In a situation where more than one eligible caregiver is present, the one most involved in the patient's care, as determined by the patient, will be the first person to be approached. If he/she declines to participate, the next most involved caregiver identified by the patient will then be approached until there are no more eligible caregivers present.

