During the patient-physician encounter, the physician will be asked to endorse question asking. Physician endorsement of question asking will be defined according to the following standardized protocol: 1) The physician asks the patient/ caregiver if they have any questions; and either 2) explains why it is important to ask questions, or 3) invites the patient/caregiver to ask questions more than once. The conversation will be recorded with a voice recorder and later transcribed. The audio-recordings will be sent via Box.com to Landmark Associates Inc. to be transcribed professionally. At the end of the consultation, the research staff who will be absent during the conversation, will ask the patient to complete the Spielberger State Trait Anxiety Inventory (**Appendix A**) again, the questionnaires assessing patients'/caregivers' views about the information material (**Appendix F**) and overall satisfaction with consultation (**Appendix G**). The questionnaires should take about 13 minutes to complete. The participating caregiver will also separately complete **Appendix F**. It should take about 5 minutes to complete. All the information materials will be collected from the participants after the consultation but those who indicate the desire to keep them will be given a copy of their forms for future use. At the end of the study, all study patients will receive a patient information booklet which also contains the GIS content. This is part of usual practice in the clinic and it will ensure that all patients get to receive identical standardized clinical care. The physician will also be asked to complete a physician assessment questionnaire (**Appendix H**) after the clinic encounter. This should take about 2 minutes to complete.

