In a subsequent open label phase to be conducted during their next follow up clinic visit at the Supportive Care Center (SCC), patients who participated in the initial blinded study will now openly receive both information materials prior seeing the physician. At the end of the visit with the physician, patients will complete a questionnaire assessing their overall preference between the two information materials. (**Appendix I**) Patients who are unable to complete the questionnaire in the clinic they will be contacted over the phone within 48 hours to complete the questionnaire. The phone call will be audio-recorded. Patients will not be provided copies of this recording. This should take approximately 2 minutes to complete.

Using a qualitative methodology, we will also conduct a descriptive exploratory repeat assessment to gain a broad understanding of patients' preferences for the information materials they receive prior to their doctor visit for the purpose of improving physician-patient communication. A sub-set of 20 patients in this study will be invited to participate in individual interviews after their follow up visits. We will purposively sample to get a range of ages, genders, ethnicities, and disease types for the interviews and match these characteristics in both treatment groups. The individual interviews will be conducted in person in a private clinic room after the physician visit by an interviewer trained in qualitative techniques (see Appendix J for interview guides). Patients who are unable to complete the interview in person will be contacted over the phone within 48 hours and requested to complete. It is anticipated that each interview will last approximately 20 minutes. At the end of each interview, the interviewer will record a field note of the circumstances and events during the interview. All interviews will be digitally recorded and professionally transcribed by Landmark Associates Inc. for analysis.

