**7. Overall patients' preference between the QPS and the GIS.**

This will be measured by the proportion of patients who would prefer to use the QPS over the GIS in communicating with their physicians after having the opportunity to use both materials. We will use a multiple choice question: *"Now that you have had the opportunity to use the two different information materials, overall, which of them would you prefer to use in communicating with your doctor?"*. Patients will select their responses from 5 options (**Appendix I**).

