### **F. STATISTICAL CONSIDERATIONS**

The primary outcome is patients' perception of helpfulness (0-10 scale) in communicating with their physicians after the first consultation visit (Appendix F, Question 4). At patient enrollment, randomization will be obtained via Clinical Trial Conduct website. A total of 136 patients will be randomized into 2 groups (QPS and GIS) in the ratio of 1:1 to reach 128 evaluable patients with 5% attrition rate due to withdrawal or lost to follow-up. With 128 evaluable patients, we will have 80% power to detect a difference in means of 2 assuming the common standard deviation of 4 using two group t-test with a two-sided significance level of 0.05. We will also reach out to patients' caregivers to collect information if available.

Standard statistics including mean, standard deviation, median, range, frequency and percentage will be summarized for variables of interest, such as patients' demographics, clinical characteristics, anxiety state, patients'/caregivers' views about the information material, patients' satisfaction, physicians' views about the information material and consultation, patients' preferences for information, patient preferences for level of involvement in decision-making and patients' overall preference between the QPS and the GIS at the follow-up visit. Two sample t- test or Wilcoxon rank sum test, whichever appropriate, will be used to compare continuous variables of interest between the QPS and the GIS. Chi-squared test or Fisher's exact test, whichever appropriate, will be used to test for associations between categorical variables and helpfulness of information material (helpful vs the rest) for each of the QPS and the GIS as well as the preference in types of information material (QPS vs GIS).

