For the primary objective and secondary objectives 2, 3, 4, 8, two sample t-test or Wilcoxon rank sum test, whichever appropriate, will be used to compare a) patients'/caregivers' perception of helpfulness in communicating with their physicians, b) patients'/caregivers' overall satisfaction with the consultation, c) physician's view/overall satisfaction about the information material and d) the change in patient anxiety state scores before and after consultation between the QPS and the GIS. For the secondary objective 5, two sample t-test or Wilcoxon rank sum test, whichever appropriate, will be used to compare the average speaking time of patient or physician during the consultation visit. Also, general linear model will be applied to assess the effect of QPS on the average speaking time adjusting for clinically and/or statistically important factors. For the secondary objective 6, univariate/multicovariate logistic regression will be used to evaluate patients' demographic and clinical factors on patients' perception of helpfulness of QPS when dichotomizing the answer to the question 3 in Appendix F ("Agree/Strongly Agree"=Helpful vs the rest). For the secondary objective 7, we will estimate the preference of information material with 95% confidence intervals. Also, univariate/multicovariate logistic regression will be used to evaluate patients' demographic and clinical factors on overall patients' preference between QPS and GIS.

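### Objective 7 (sheet preference) is planned as one overall proportion and modelled without randomised arm, so preference for the question prompt sheet cannot be told apart from preference for the sheet used first

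*Protocol*

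**What the plan says.** Objective 7 in section A reads "To examine the overall patients' preference between the QPS and GIS in an open label phase". Outcome 7 in section E9 makes this a single quantity: "This will be measured by the proportion of patients who would prefer to use the QPS over the GIS in communicating with their physicians".

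Section F gives the analysis in two parts. The first is "we will estimate the preference of information material with 95% confidence intervals". The second is "univariate/multicovariate logistic regression will be used to evaluate patients' demographic and clinical factors on overall patients' preference between QPS and GIS". Section F also plans chi-squared or Fisher's exact tests of preference against categorical variables that it does not name.

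Section E6 fixes the exposure history. At the first visit: "The patient will then be randomized to receive either the QPS" or the GIS. The sheets are collected afterwards, but "those who indicate the desire to keep them will be given a copy of their forms for future use". At the next follow-up visit, "patients who participated in the initial blinded study will now openly receive both information materials prior seeing the physician", and preference is asked after that consultation. E6 also gives every patient a booklet containing the GIS content at the end of the study, a time point not tied to a visit.

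No section gives preference by first-visit arm, puts arm in the preference model, or mentions familiarity, order or carry-over. The one provision by arm in the open-label phase is the matching of characteristics between treatment groups for the 20 interviewees.

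**The concern.** When asked for a preference, each patient has already taken one of the sheets through an earlier consultation. Which one was set by randomisation and is on record for everybody. First use may well affect the later choice, yet the planned estimate and models leave it out.

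What is at stake is the reading of the result. Suppose 60% prefer the QPS. That could come from 60% in both arms, which supports the sheet itself. It could also come from 80% among those who used the QPS first and 40% among those who used the GIS first, which says that patients largely favour what they know. One overall proportion looks the same in both cases.

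The protocol's own text also makes unequal familiarity effects conceivable. Copies go only to patients who ask for them. If the booklet with the GIS content reaches patients before the follow-up visit, QPS-first patients may have seen both contents, while GIS-first patients would not yet have seen the QPS.

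**Working it through.** **Inputs from the protocol (section F).** 136 patients randomised 1:1, 128 evaluable, so 64 per arm. This size serves the primary outcome: a difference of 2 with SD 4 at 64 per arm gives t-test power 0.801, so the plan's figure reproduces. It does not bear on objective 7, for which no precision target or return rate is stated. I use 64 v 64 as the best case.

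**Assumptions.** The documents give no familiarity effect. Let p be the QPS preference without familiarity, f1 the shift towards the QPS in the QPS-first arm, and f2 the shift towards the GIS in the GIS-first arm, with n1 and n2 patients answering.

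- Overall proportion = [n1(p + f1) + n2(p − f2)] / (n1 + n2)
- Equally weighted average = p + (f1 − f2)/2
- Difference between arms = f1 + f2

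**1. Symmetric effect, equal return.** p = 0.50, f1 = f2 = 0.10, 64 v 64: (64 × 0.60 + 64 × 0.40)/128 = 50.0%. There is no bias, but the arms stand at 60% and 40%.

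**2. Symmetric effect, unequal return.** p = 0.50, 64 v 40. With f = 0.10: (38.4 + 16.0)/104 = 52.3%. For f = 5, 10, 15 and 20 points the overall figure is 51.2%, 52.3%, 53.5% and 54.6%. The equally weighted average stays at 50%.

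**3. Asymmetric effect, equal return.** p = 0.50, 64 v 64:

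| Effect | Overall | Equally weighted |
|---|---|---|
| 10 points, QPS-first arm only | 55% | 55% |
| 20 points, QPS-first arm only | 60% | 60% |
| 20 points, GIS-first arm only | 40% | 40% |

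Equal weighting does not help here.

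**4. A second return pattern.** Assume 70% prefer the QPS in the QPS-first arm and 50% in the GIS-first arm, so the equally weighted figure is 60%.

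- 50 v 35 returning: (35 + 17.5)/85 = 61.8%
- 55 v 25 returning: (38.5 + 12.5)/80 = 63.8%

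With 136/2 = 68 randomised per arm, the second pattern means return of 55/68 = 81% against 25/68 = 37%, which is extreme.

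**5. Precision (Wald 95% half-widths).**

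- Overall, n = 128, p = 0.50: 1.96 × √(0.25/128) = 8.7 points
- One arm, n = 64: 1.96 × √(0.25/64) = about 12 points
- Equally weighted, 64 v 64: 1.96 × ½ × √(0.25/64 + 0.25/64) = 8.7 points, the same as overall
- Step 4 overall figures: 10.3 points at n = 85 and 10.5 at n = 80

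So the shifts of 1.8 and 3.8 points in step 4 are about one-sixth and one-third of the half-width. A 20-point effect in one arm (step 3) moves the estimate by 10 points, more than the 8.7-point half-width.

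**6. Can the arm split show anything?** At 64 per arm, the power to detect a difference between arms is about 0.62 for 60% v 40% and 0.93 for 65% v 35%. Large familiarity effects would show; small ones might not.

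**The case against.** Several counter-arguments have force.

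- **Detail for the analysis plan.** A table by arm and a covariate list for an exploratory model often belong in an SAP, which is not at hand and may add arm. This stands in part. But section F does not leave objective 7 open: it names the estimate and the class of covariates. For objective 5 it allows adjustment for clinically or statistically important factors generally; for objective 7 it names demographic and clinical factors only, and arm is neither.
- **Other text could cover arm.** Arm could be among the unnamed categorical variables, and section F closes by allowing other methods. So a reader might infer that the arm difference will never be reported, and the document does not establish that. Still, a chi-squared test supplies neither arm-specific estimates nor an adjusted model.
- **Randomisation protects the overall figure.** True for a symmetric effect with balanced return (step 1). Nothing in the protocol suggests that return will differ by arm, and telephone completion within 48 hours is offered to patients who cannot complete the form in clinic.
- **Predictor models.** A reader might infer that leaving arm out confounds the demographic and clinical predictors. Arm is randomised, so in expectation it is independent of baseline factors among those enrolled; the expected effect is mainly a modest attenuation of odds ratios. Nor do the documents show that arm is a major determinant of preference.
- **Sequential use is part of the measure.** Outcome 7 asks for preference once both sheets have been available. That is so, but it does not remove the need to know whether the answer depends on which came first.

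**Conclusion.** The point holds as a gap in the planned analysis of a secondary objective. Objective 7 has one overall estimate and models that omit a randomised design factor already recorded for every patient.

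It is tempting to conclude that the overall preference will be biased by familiarity. The documents do not support that. Bias needs either an asymmetric effect or unequal return by arm, and the protocol gives no figure for either. Under the assumptions above, unequal return alone moves the estimate by about 1 to 5 points, well inside the interval. A one-arm effect of 10 to 20 points moves it by 5 to 10 points, and only the upper end exceeds the half-width of 8.7 points. What holds in every scenario tried is that a difference between arms (10 to 40 points in steps 1 to 3) would be hidden in the single figure.

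The primary comparison is made after the first visit and is not touched.

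**What to change.** In section F, under objective 7:

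1. Report the proportion preferring the QPS with a 95% confidence interval separately by randomised arm, together with the number completing the follow-up questionnaire in each arm.
2. Give the equally weighted average of the two arms as the overall figure. State that this removes dependence on unequal return only. It does not correct an asymmetric familiarity effect or selective return within an arm; the arm-specific figures serve to reveal a difference.
3. Include randomised arm as a covariate in the preference logistic models.

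This costs a few sentences, with no new data and no added burden for patients. Arm-specific intervals are wider, about 12 points half-width at 64 per arm against 8.7 overall. The equally weighted average costs no precision when return is equal and little when it is not: in the 55 v 25 case its half-width is 1.96 × ½ × √(0.21/55 + 0.25/25) = 11.5 points, against 10.5. The arm comparison should be presented as estimation, since the trial is not powered for it.

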#### **G. DATA CONFIDENTIALITY PROCEDURES**

Health information will be protected and we will maintain the confidentiality of the data obtained from the database to the best of our ability.

**Collection of identifiers:** We will collect and securely store patients' identifiers (name and medical record number). Each patient will be assigned a study number that will be the only identifier to figure in the analytical file and personal data will not be disclosed in any form. The key linking these numbers will be retained in a securely locked file by the investigator.

**Data Storage:** Strict safeguards will be in place to protect participant privacy and data confidentiality. All electronic records will be stored on password-protected institution computers behind the institution firewall. Paper records will be stored in a locked cabinet in a locked office located in the Department of Palliative, Rehabilitation, and Integrative Medicine. Audiotapes will be digitally stored indefinitely and will include voice identifiers and study ID.

**Training of personnel:** Only MDACC personnel trained in maintaining confidentiality will have access to study records.

**Data sharing:** Landmark Associates Inc. will receive de-identified audio-recordings via Box.com to assist with professional transcription. Box.com is a password-protected content management and file sharing system behind the institution firewall.

**Final disposition of study records:** The data may be maintained indefinitely, aggregated in the future, and used for future research studies.

Audio recordings will be sent via secure and encrypted MD Anderson Outlook e-mail to participants upon request. We will utilize the encrypted e-mail method (“[send secure]”) to send the recordings to participants, as suggested by our Institutional Compliance Office.

